**Figure 2 F2:**
[figure not shown]
Trial schema. VITTAL, Viability testing and transplantation of marginal livers.

### Analysis of outcome measures

#### Primary analysis

To assess (A) the feasibility of NMP-L, the rescue rate will be calculated as the number of perfused marginal grafts meeting the criteria for viability (numerator) divided by the total number of perfused marginal grafts (denominator).

$$Rescue\;Rate=\frac{Number\;of\;viable\;perfused\;marginal\;grafts}{Total\;number\;of\;perfused\;marginal\;grafts}$$

To assess (B)—achievement of successful transplantation of previously rejected donor liver following viability testing using NMP-L. We will evaluate 90-day patient survival rate as an indicator of liver function and/or viability following transplantation of marginal liver grafts following NMP-L. The 90-day patient survival rate will be calculated as the number of patients alive at 90-day post-transplant with a VITTAL graft, divided by the total number VITTAL patients transplanted.

$$90\;day\;patient\;survival\;rate=\;\frac{Number\;of\;patients\;alive\;at\;90\;days\;post\;transplantation}{Total\;number\;of\;transplanations\;performed}$$

For (A), all livers undergoing NMP-L treatment will be included for evaluation in the interim and final analyses. For (B), all transplantations performed will be included for evaluation in the interim and final analyses. The rate outcomes will be reported together with confidence intervals using the Wilson (1927) method.^43^

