### Graft entry into study and subsequent preparation

The patient and donor liver pathways can be seen in figure 1. All livers will be retrieved with the intention and standardised technique to use them for transplantation. Following the retrieval procedure at the donor hospital the liver will be placed in ice-cold preservation solution on the back table and transported (according to local protocol). If the liver is allocated to UHBFT, if it is then considered not suitable for use it must be rejected by the on-call transplanting surgeon. For the liver to be considered untransplantable, the liver will be inspected by the on-call transplant surgeon and another transplant surgeon in the department. The liver will then be offered as a fast track graft to the other centres around the UK. If rejected by all centres and if consent for research was taken, it will be considered for use in VITTAL. Livers offered to our unit as fast track offers from other centres will undergo the same two-consultant rejection process. An appropriate consented potential recipient will be selected by the transplant surgeon and contacted by the coordinator and will come into hospital for admission. The coordinator will request three units of packed red blood cells, matched to the intended recipient, for use in the OrganOx metra device. The liver will be prepared according to the procedure for preparing the device for use and placing the organ on the device (described in detail in the OrganOx metra Instructions for Use (IFU) document (V.13.0, 12 March 2016). The liver will be weighed prior to being connected to the device. If cannulation proves impossible, the liver will be rejected as previously intended. If the liver meets the criteria for transplantation, the recipient explantation will commence and the procedure for removing the liver from the device is also described in the IFU. Implantation and reperfusion of the liver will proceed as per the usual practice of the implanting centre. The patient will be clerked as if they were being admitted for a standard liver transplant.

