## Objectives and outcome measures

### Primary

There are two linked primary objectives and respective outcome measures:

Primary objective: (A) Establish the feasibility of NMP-L to increase the number of transplantable livers.

Primary Outcome measure: (A) ‘Rescue rate’ that is, the proportion of rejected livers that can be used for transplantation having been deemed viable following a period of machine perfusion.

Primary objective: (B) Achieve successful transplantation of previously rejected donor livers following viability testing using NMP-L.

Primary outcome measure: (B) 90-day patient survival, calculated as the number of patients alive 90-day post-NMP-L-treated marginal liver transplantation (numerator) divided by the total number of NMP-L-treated marginal liver transplants performed (denominator).

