## Statistical justification and outcome analysis

### Sample size justification

For (A) feasibility of NMP-L to rescue discarded liver grafts, it is anticipated that NMP-L will achieve a desirable organ recovery rate of at least 50%, with an undesirable rate of 30% or less as this would not be considered economically feasible. The significance level (α) is set at 0.05, corresponding to the probability of incorrectly rejecting the hypothesis given it is true (type I error), and the power is set at 0.90 (type II error rate, β=0.10), corresponding to the probability of correctly deciding the NMP-L treatment is successful given the true response rate is greater than 50%.

Using a Simon’s two-stage design^38^:

Interim assessment stage 1A of accrual: 24 marginal grafts will be perfused and assessed in the first stage. Grafts will be transplanted depending on the criteria achieved. The procedure will be considered infeasible if there are fewer than eight recovered livers. If more than eight livers are transplanted, we will proceed to Stage 2A.

Final stage 2A of accrual: Up to additional 29 marginal grafts will be perfused. We would consider the procedure feasible if there are at least 22 recovered livers out of 53 perfused livers.

For (B) for viable livers transplanted following NMP-L, a desirable 90-day patient survival rate is at least 88%, with an undesirable rate of 73% (15% lower). The mean 90-day patient survival rate for ‘standard’ liver transplants is 93%.^42^ An optimal three-stage design^39^ will be used to test the null hypothesis that the mean 90-day patient survival rate will be less than 73% (p≤0.73) versus an alternative hypothesis that the 90-day patient survival rate will be at least 88% (p≥0.88). The significance level is set at 0.20 (target α=0.2), giving a 0.2 probability to conclude that a single transplantation is viable when it truly is not viable. The power is set at 80% (target β=0.2), giving a 0.2 probability to conclude that a single transplantation is not viable when it truly is viable.

Interim assessment stage 1B: Following transplantation in three patients, the trial will stop early (concluding p≤0.73) if there are fewer than two patients achieving 90-day survival. If two or more patients reach the primary end point of 90-day survival, an additional eight transplantations will be performed.

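### The co-primary rescue rate counts viable livers, but the stage 1A rule for continuing counts transplanted ones

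*Protocol article*

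**What the plan says.** All places are in the Protocol article.

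- **Outcome definition** (Objectives and outcome measures, Primary): the rescue rate is "the proportion of rejected livers that can be used for transplantation having been deemed viable following a period of machine perfusion".
- **Analysis formula** (Primary analysis): the rate is "the number of perfused marginal grafts meeting the criteria for viability (numerator) divided by the total number of perfused marginal grafts (denominator"). The same section evaluates every liver that undergoes NMP-L.
- **Design** (Sample size justification): a Simon two-stage test of "a desirable organ recovery rate of at least 50%, with an undesirable rate of 30% or less", with these terms: "The significance level (α) is set at 0.05"; power 0.90; "24 marginal grafts will be perfused and assessed in the first stage", then up to 29 more.
- **Stage 1A stop and final rules** (same section): NMP-L is judged infeasible when the recovered livers number below eight, and feasible when at least 22 of 53 perfused livers are recovered.
- **Stage 1A rule for continuing** (same section): "If more than eight livers are transplanted, we will proceed to Stage 2A".
- **Livers that never reach perfusion** (Graft entry into study and subsequent preparation): "If cannulation proves impossible, the liver will be rejected as previously intended".

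**The concern.** One interim decision rests on two different counts. Stopping depends on recovered livers and continuing on transplanted livers. Viability and transplantation are separate events: the recipient's operation starts only after the surgeon is satisfied that the criteria are met, so a viable liver can still go unused, for example for reasons on the recipient's side. Such a liver is a success in the rescue rate and a non-success for continuing. The plan also assigns no decision when eight or more livers are recovered but no more than eight are transplanted.

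The count affects the operating characteristics. The stated alpha and power hold only if the same event is counted at both stages. A stricter event at the first gate makes it more likely that a workable technique stops early.

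The denominator wording is a lesser matter. The outcome definition names rejected livers, while the design and the formula use perfused livers. A liver that cannot be cannulated lies between the two.

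**Working it through.** **Inputs from the Sample size justification:** p0 = 0.30, p1 = 0.50, n1 = 24, n2 = 29, final cut-off 22 of 53.

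**Assumed input:** t, the share of viable livers not transplanted. The documents give no figure. I use 5% and 10%.

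**1. Reproduce the design, one count at both stages.** With X ~ Bin(24, p) and Y ~ Bin(29, p),

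Pr(declare feasible) = Σ over x ≥ g of Pr(X = x) · Pr(Y ≥ 22 − x).

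| Gate g | at p = 0.30 (alpha) | at p = 0.50 (power) |
|---|---|---|
| 8 (stop at 7 or fewer) | 0.0466 | 0.9017 |
| 9 (literal reading of the rule for continuing) | 0.0419 | 0.8734 |

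A gate of eight meets both targets; a gate of nine misses the power target. A search over two-stage designs found none with a total of 51 or 52 that meets both limits. Among those with a total of 53, the plan's design (24 livers, stop at 7 or fewer) has the smallest expected size. The intended gate is therefore eight.

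**2. Count transplants at the stage 1A gate only.** This is what the text says, since the final rule counts recovered livers. Given X viable livers, the number transplanted is T ~ Bin(X, 1 − t). Then

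Power = Σ over x of Pr(X = x) · Pr(T ≥ g | X = x) · Pr(Y ≥ 22 − x), at p = 0.50.

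| t | g = 8 | g = 9 |
|---|---|---|
| 0% | 0.902 | 0.873 |
| 5% | 0.886 | 0.840 |
| 10% | 0.862 | 0.792 |

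The same sum at p = 0.30 and g = 8 gives 0.044 (t = 5%) and 0.041 (t = 10%), so the mixed count costs power and does not raise the type I error.

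**3. Check the denominator.** The Study design overview, the Sample size justification and the Primary analysis all use perfused livers, so the alpha and power in step 1 apply to the formula as written. Non-perfused livers change only the descriptive rate. At the cut-off, 22/53 = 41.5%; with 1, 3 or 6 further livers in the denominator it is 22/54 = 40.7%, 22/56 = 39.3% or 22/59 = 37.3%.

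**4. Check the alternative denominator.** Suppose 8 of 24 and 22 of 53 were kept, every liver taken for the trial were counted, and the rate among perfused livers were 50%. If a share u is never perfused, the success rate is 0.50(1 − u), and power is 0.875, 0.826 or 0.721 for u = 2%, 5% or 10% (u is also an assumption).

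**The case against.** The best defence is that the word for transplanted is loose drafting. The abstract treats viable livers as livers that are transplanted, and a consented recipient is called in for each one. Two of the three decision rules already say recovered, and an article condenses the full protocol. If every viable liver is implanted, the counts coincide. This stands as an argument about size: the loss is small if few viable livers go unused. It does not remove the conflict, because the article itself prints both the formula and the decision rule.

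Two stronger readings are tempting, and the documents do not support either.

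- **Type I error.** A reader might infer that leaving out livers that cannot be cannulated inflates the error rate. If 30% were the true rate per liver taken for the trial, and 2%, 5% or 10% of those were never perfused, the chance of declaring feasibility would be 0.057, 0.077 or 0.126. But the protocol states its hypothesis per perfused liver and gives no such share. Nor does it say that a liver that cannot be cannulated has already entered the trial. A liver that fails during perfusion stays in the denominator.
- **Larger power loss.** A reader might apply the transplant count at both stages and obtain 0.826 or 0.721 for t = 5% or 10%. The final rule counts recovered livers, so these figures do not apply.

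The outcome definition can also be read as already limited to perfused livers, since it ends with machine perfusion. That is a fair reading, so its wording needs only alignment.

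**Conclusion.** The inconsistency in the numerator is real and sits inside a go/no-go rule for a co-primary outcome. Its cost is a moderate loss of power: about 1.5 points (0.902 to 0.886) or 4 points (0.902 to 0.862) at a gate of eight, for 5% or 10% of viable livers untransplanted. Under the literal gate of nine, power is 0.840 or 0.792, and part of that shortfall comes from the separate gap at exactly eight (baseline 0.873). These sizes rest on the assumed shares and on each viable liver being transplanted independently with the same probability.

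The perfused denominator is coherent with the test, and its alpha and power hold. The perfused-only rate exceeds a rate per liver taken for the trial only to the extent that unperfused livers occur, and the documents give no figure for that.

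**What to change.** 1. In the Sample size justification, count livers that meet the viability criteria at both stages: continue at 8 or more of 24, feasible at 22 or more of 53. This matches the Primary analysis and also settles the case of exactly eight.
2. Keep perfused livers as the denominator, and reword the outcome definition so that it names perfused rather than rejected livers.
3. Report viable but untransplanted livers separately, with reasons.
4. Report livers taken for the trial but not perfused, such as failed cannulations, separately. Add a sensitivity rate that counts them as not rescued.

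Items 1 and 2 are wording only; they restore alpha 0.0466 and power 0.9017 with no change in sample size. Items 3 and 4 need a log of every liver taken for the trial; the article does not say whether the liver registration form already captures those that cannot be cannulated. Making all such livers the primary denominator would not be a wording change: it alters the estimand and, with the cut-offs unchanged, lowers power as in step 4 of the working, so the sample size would have to be rechecked.

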Interim assessment stage 2B: Following transplantation in 11 patients (combined first and second stages) the trial will stop early (concluding p≤0.73) if there are 7 or fewer successes. If 8or more patients reach the primary end point, an additional 11 transplantations will be performed.

Final stage 3B: Following transplantation in 22 patients in all three stages, the trial will be successful if at least 18 patients reach the primary end-point of 90-day survival.

The trial schema is provided in figure 2.

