#### Planned interim assessments

As we have used adaptive designs, there are planned formal interim assessments for both (A) feasibility of NMP-L and (B) successful transplantation of rescued livers, with clear ‘Go’/‘No go’ decisions as detailed earlier. Ideally, recruitment (ie, transplantation) would stop while interim analyses of the primary outcome measures are performed. For (A), this could happen immediately, however for (B), this would result in a pause of over 3 months hence the pragmatic approach for such adaptive designs is to continue recruitment while they are being conducted.

To maximise patient safety, for (B) at the end of the first stage (transplantation of the first three patients), recruitment will be paused to allow the Data Monitoring Committee (DMC) to assess the initial safety data. Once all three patients are discharged, if the DMC considers the patients to be recovering well, with liver function that would be expected at this stage, recruitment can continue prior to the patients reaching the primary endpoint of 90-day survival. A follow-on report will be sent to the DMC once the third patient reaches the primary end-point. For the second stage (transplantation of 11 patients), safety data will be sent to the DMC for review after discharge of all 11 patients however recruitment need not stop at this point. A follow-on report will again be sent once the 11th patient reaches the primary end-point.

Additional DMC meetings will be conducted on request if the success criteria are not met. If recruitment is fast, prompt reviews will be necessary to ensure the use of interim decisions.

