#### Secondary analysis

For all secondary outcome measures, analyses will be mainly descriptive. Continuous exploratory measures will be summarised via means, medians, SD and ranges. Categorical measures will be summarised with number and proportion in each category. To model repeated measures over time (eg, QoL), a linear mixed effects model (considering subject correlation) using parametric and more flexible models may be considered. Time-to-event outcomes will be assessed using the method of Kaplan and Meier. Median survival with corresponding 95% CI will also be reported where appropriate. The assessment of graft function post-transplantation by incidence of primary non-function and early allograft dysfunction will be carried out by comparing results with a contemporary matched recipient group of patients obtained from a prospectively maintained database, with adjustment for potential confounders.

The contemporary matched recipient group will be matched using the following:Patient characteristics: age, sex, BMI, model for end-stage liver disease (MELD), UK end-stage liver disease (UKELD), aetiology;Donor liver characteristics: DCD or DBD, sex.

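### Fixed-sample Wilson intervals and raw proportions are planned for rates from multi-stage stopping designs; for 90-day survival, coverage of a 95% interval can fall to about 85%

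*Protocol article*

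**What the plan says.** Under Primary analysis, the protocol article defines each primary rate as a simple proportion: viable livers over livers perfused (A), and patients alive at 90 days over transplants performed (B). It then fixes the interval: "The rate outcomes will be reported together with confidence intervals using the Wilson (1927) method". No confidence level is attached. The only level named in the article is in Secondary analysis, for a different quantity: "Median survival with corresponding 95% CI will also be reported where appropriate".

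The denominators are not fixed. Planned interim assessments says "As we have used adaptive designs, there are planned formal interim assessments" for both components. Under Sample size justification:

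- **B** tests 0.73 against 0.88 in three stages. After 3 transplants, "the trial will stop early (concluding p≤0.73) if there are fewer than two patients achieving 90-day survival". After 11, "the trial will stop early (concluding p≤0.73) if there are 7 or fewer successes". After 22, success needs at least 18 survivors. The targets read "The significance level is set at 0.20 (target α=0.2" and "The power is set at 80% (target β=0.2".
- **A** tests 30% against 50% in two stages. After 24 livers, fewer than eight recovered means infeasible. After 53, at least 22 recovered means feasible. The targets are alpha 0.05 and power 0.90.

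Neither the estimate nor the interval is adjusted for this staged stopping.

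**The concern.** In a design that stops only for poor results, a small final sample is itself a sign of a bad run. The raw proportion then averages below the truth. A fixed-sample interval around an early-stop result is also centred too low, and its upper limit can fall below the true rate. With a first look at only 3 patients this could matter for B.

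The estimates and error bars for the two co-primary outcomes are at stake. The article's Summary intends the data to inform acceptance and allocation of high-risk livers, so readers will rely on those figures. The choice of method is made in the article itself and is not left to another document.

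**Working it through.** **Inputs.** Stage sizes, boundaries, hypotheses and error targets come from Sample size justification; the interval method comes from Primary analysis. Three assumptions are mine: a two-sided 95% level, stopping exactly at 3, 11 or 24 when the rule is met, and continuation of A at exactly 8 of 24.

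**Reproducing the design.** Each stage adds independent binomial outcomes, and paths below a boundary are removed.

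- A (continue at ≥8/24, success at ≥22/53): alpha 0.0466, power 0.9017. This agrees with 0.05 and 0.90.
- B (≥2/3, ≥8/11, ≥18/22): alpha 0.2340, power 0.8566. The stated alpha of 0.20 is not reproduced; this matters for the fix.

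**Formulas.** For a final result of x successes in n:

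- Wilson limits = [p̂ + z²/(2n) ± z√(p̂(1−p̂)/n + z²/(4n²))] / (1 + z²/n), with p̂ = x/n and z = 1.96
- coverage(p) = sum of P(n, x | p) over all final results whose interval contains p
- bias(p) = sum of (x/n)·P(n, x | p), minus p

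**Wilson limits at early stops in B.** 1/3 gives 6.1% to 79.2%; 7/11 gives 35.4% to 84.8%. Both upper limits lie below the 88% target.

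**Worked case, B at p = 0.85.** Both of those upper limits are below 0.85, as are those for lower counts, so every early stop misses.

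- P(stop at 3) = 0.15³ + 3 × 0.85 × 0.15² = 0.0034 + 0.0574 = 0.0608
- P(stop at 11) = 0.0473
- misses among trials reaching 22 = 0.0422
- total misses = 0.0608 + 0.0473 + 0.0422 = 0.150, so coverage is 85.0%

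**Results for B.**

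| True survival | Wilson coverage | Bias of raw rate (points) | Probability of reaching 22 | Coverage among those reaching 22 |
|---|---|---|---|---|
| 0.73 | 95.2% | −8.2 | 60.4% | 98.4% |
| 0.80 | 85.9% | −5.4 | 78.9% | 98.7% |
| 0.85 | 85.0% | −3.4 | 89.2% | 95.3% |
| 0.88 | 91.4% | −2.2 | 93.7% | 97.6% |

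The minimum is 84.8%, at 0.849. With a fixed 22 patients the Wilson minimum over 0.73 to 0.88 is 92.5%, so most of the loss comes from stopping and not from Wilson's small-sample behaviour.

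**Results for A.** Coverage is 92.3% at 0.45 and 92.4% at 0.50, with a minimum of 92.1% at 0.494. Bias at 0.50 is −0.4 points.

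**A design-based alternative.** An exact 95% interval with stage-wise ordering (later stage ranks higher, then more successes) covers at least 95.1% for B over 0.50 to 0.99.

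| Result (B) | Stage-wise exact 95% | Wilson 95% |
|---|---|---|
| 1/3 | 0.8% to 90.6% | 6.1% to 79.2% |
| 7/11 | 32.4% to 91.9% | 35.4% to 84.8% |
| 18/22 | 60.1% to 95.2% | 61.5% to 92.7% |
| 20/22 | 70.9% to 98.9% | 72.2% to 97.5% |

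**Interval against decision rule.** At 18, 19 and 20 of 22, which are all successes, both kinds of 95% interval include 73%. At 22/53 both include 30% (Wilson 29.3% to 54.9%, stage-wise 28.3% to 56.3%). At levels matching the one-sided alphas:

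- A, 95% lower bound at 22/53: Wilson 31.1%, stage-wise 30.2%. Both exclude 30%.
- B, 80% lower bound at 18/22: Wilson 73.9%, stage-wise 71.9%. The stage-wise bound falls below 73% because the printed rules have alpha 0.234, not 0.20.

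**The case against.** The strongest reply is that nothing is decided by these intervals. Success and futility are fixed counts, and the intervals are only reported beside the rates. That stands: error rates and go/no-go decisions do not change.

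A reader might infer that Wilson contradicts the decision rule, because an 18/22 success would carry an interval containing the 73% just rejected. The documents do not support blaming the method. The overlap comes from setting an assumed two-sided 95% level beside tests that are one-sided by construction at 0.20 and 0.05. The stage-wise 95% interval overlaps in the same way, and Wilson at the matching level does not.

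A reader might also infer that both primary rates are seriously misreported. For A the shortfall is about 3 points of coverage. For B, trials that reach 22 patients have Wilson coverage of 95% to 99% at the four rates checked, and at 0.88 about 94% of trials get there.

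Finally, Planned interim assessments allows recruitment to continue while 90-day results mature, so a stopped trial could hold more than 3 or 11 patients. This could soften the loss: with no stop at 3, minimum coverage is 88.5%. It does not remove it, because the sample size would still depend on results. None of these replies makes the fixed-sample interval right for B after an early stop.

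**Conclusion.** The point holds as a reporting defect, mainly for B. At an assumed 95% level with stopping at the printed boundaries, Wilson coverage for 90-day survival drops to about 85% in the worst case and is 91% at the design alternative. The raw rate is too low on average by 2.2 to 8.2 points between 0.88 and 0.73. The 85% is a worst case, not typical across all survival rates. A is only slightly affected.

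The unstated confidence level is a second and separate issue. At 95%, some declared successes would appear beside intervals that include the rejected rate, whichever of the two interval methods is used.

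**What to change.** 1. For the primary rates, chiefly B, replace the raw proportion and Wilson interval with the uniformly minimum-variance unbiased estimate and an exact interval that respects the multi-stage sample space. Compute both for the stage sizes actually realised, since recruitment may run past an interim look. Keep Wilson for secondary proportions.
2. State the confidence level, and add a one-sided lower bound at each design's alpha (95% for A, 80% for B), so that the bound and the success rule refer to the same test.
3. For B, reconcile the printed boundaries with the stated alpha of 0.20 at the same time. As printed, the 80% stage-wise bound at 18/22 (71.9%) disagrees with the success rule.

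The cost is some wording and a few lines of code, plus wider intervals. The widening is slight near the success boundary but large after an early stop: 32% to 92% at 7/11, against 35% to 85% for Wilson. Stage-wise ordering can also behave oddly at low final counts. At 8/22 it gives 39.9% to 91.9%, which excludes the observed 36.4%. Another exact ordering may therefore be preferred, and whichever is used should be named in advance.
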